## 9.4 Populations for Analyses

For purposes of analysis, the analysis sets in [Table 3](#) are defined.

**Table 3 Analysis Sets**

| Analysis Set                       | Description                                                                                                                                                                                                                                                                                                            |
|------------------------------------|------------------------------------------------------------------------------------------------------------------------------------------------------------------------------------------------------------------------------------------------------------------------------------------------------------------------|
| Intention to Treat (ITT)           | All patients who are randomised and match the inclusion/exclusion criteria of the Master Protocol and relevant sub protocol.                                                                                                                                                                                           |
| Safety Set                         | All patients who are randomised and take at least 1 dose of study medication.                                                                                                                                                                                                                                          |
| Pharmacokinetic Analysis Set (PKS) | All patients who are randomised and take at least 1 dose of the candidate agent and have quantifiable candidate agent concentrations postdose without protocol deviations or events affecting the pharmacokinetic results.                                                                                             |
| Pharmacodynamic Analysis Set (PDS) | All patients who are randomised and take at least 1 dose of study medication (candidate agent or standard of care) and have evaluable results for at least 1 pharmacodynamic endpoint postdose. All analyses of the PDS will be based on each patient's randomised assigned treatment (not actual treatment received). |

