##### Analysis sets:

- **Intention to Treat (ITT):** All patients who are randomised and match the inclusion/exclusion criteria of the Master Protocol and relevant sub-protocol will be included in the ITT.
- **Safety Set:** All patients who are randomised and take at least 1 dose of study medication will be included in the safety set.

- Pharmacokinetic Analysis Set (PKS): All patients who are randomised and take at least 1 dose of the candidate agent and have quantifiable candidate agent concentrations postdose without protocol deviations or events affecting the pharmacokinetic results will be included in the PKS.
- Pharmacodynamic Analysis Set (PDS): All patients who are randomised and take at least 1 dose of study medication (candidate agent or SoC) and have evaluable results for at least 1 pharmacodynamic endpoint postdose. All analyses of the PDS will be based on each patient's randomised assigned treatment (not actual treatment received).

Efficacy, safety, pharmacokinetic, and pharmacodynamic results will be listed and summarised by stage, dose, and scheduled time for the respective analysis sets, where appropriate. Candidate agent concentration versus response variables may be graphically displayed for selected endpoints.

Exposure-response data obtained from this study may be combined with data from other studies and used for modelling and simulations.

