## 5.0 STUDY POPULATION

Prospective approval of protocol deviations to recruitment and enrolment criteria, also known as protocol waivers or exemptions, is not permitted.

The inclusion and exclusion criteria listed below may be supplemented by additional criteria stipulated in the sub-protocols that are specific to the target candidate being tested (eg, criteria related to prohibited medications). In order to enrol, a patient or legally authorised representative must sign an informed consent form (ICF) and meet all entry criteria for both the Master Protocol and at least 1 respective sub-protocol.

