### 5.2 Exclusion Criteria

Patients are excluded from the study if any of the following criteria apply (or any of the criteria from the appropriate sub-protocol):

1. Patients who have previously had a score of 6 or 7 on the 9-point ordinal scale.
2. Any patient whose interests are not best served by study participation, as determined by a senior attending clinician.
3. Alanine aminotransferase (ALT)/aspartate aminotransferase (AST)  $> 5 \times$  the upper limit of normal (ULN).

4. Known active infection with HIV or hepatitis B or C.
5. Stage 4 severe chronic kidney disease or requiring dialysis (ie, estimated glomerular filtration rate  $<30$  mL/min/1.73 m^2).
6. History of the following cardiac conditions:
  - a) Myocardial infarction within 3 months prior to the first dose
  - b) Unstable angina
  - c) History of clinically significant dysrhythmias (long QT features on electrocardiogram [ECG], sustained bradycardia [ $\leq 55$  bpm]), left bundle branch block, cardiac pacemaker or ventricular arrhythmia) or history of familial long QT
7. Screening 12-lead ECG with a measurable QTc interval according to Fridericia correction (QTcF)  $>500$  ms.
8. Anticipated transfer to another hospital that is not a study centre within 72 hours.
9. Allergy to any study medication.
10. Experimental off-label usage of medicinal products as treatments for COVID-19.
11. Patients participating in another clinical study of an investigational medicinal product.
12. Active tuberculosis defined as requiring current treatment for tuberculosis.

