### **6.3 Measures to Minimise Bias: Randomisation and Blinding**

No blinding will be used in this study.

The study will randomise participants on an ongoing basis to receive either one of the active candidate treatment arms as an add-on to SoC or to receive SoC alone. Randomisation will be stratified by study centre and baseline severity grade.

If additional arms (candidate treatments) are added to or dropped from the study, randomisation will proceed with an equal probability of assignment to each of the remaining arms, except for situations where a patient does not meet the inclusion/criteria for, and hence would be excluded from, one or more of the sub-protocols.

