| Primary     | 
Stage 1:
 
Time to 2-point improvement on the 9-point ordinal scale, live discharge, or fit for discharge (as analysed at Day 29), whichever comes first, will be compared with each treatment arm with standard of care (SoC) using log-rank test at the one-sided 0.1 alpha level. Patients in the Stage 1 Intention to Treat (ITT) set will be used.
 
Stage 2:
 
The time to 2-point improvement on the 9-point ordinal scale, live discharge, or fit for discharge (as analysed at Day 29), whichever comes first, analyses will be conducted between the selected treatments plus SoC and SoC alone. The primary endpoint could be re-determined based on Stage 1 results. Patients in the Stage 2 ITT set will be used for the following analyses:
 
The time to 2-point improvement on 9-point ordinal scale, live discharge, or fit for discharge at Day 29 will be conducted between each selected treatment group and control using the log-rank statistic, stratifying for study centre and baseline severity grade, and the p-value associated with the log-rank statistic will be compared at the 2-sided 0.05 alpha level. The hazard ratio between treatment arm and SoC will be estimated using Cox regression, including treatment, age category (age <70 years vs ≥70 years), baseline severity, age category and treatment interaction, baseline severity and treatment interaction as fixed effect, and study centre as random effect.
 |

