## **Appendix 2           Regulatory, Ethical, and Study Oversight Considerations**

### **Protocol Compliance**

The Investigator agrees to comply with the requirements of the Protocol and Good Clinical Practice. Prospective, planned deviations or waivers to the protocol are not allowed under the UK regulations on Clinical Trials and must not be used; eg, it is not acceptable to enrol a patient if they do not meet the eligibility criteria or restrictions specified in the protocol.

Accidental protocol deviations can happen at any time. They must be adequately documented on the relevant forms and reported to the Chief Investigator and Sponsor immediately.

Deviations from the protocol, which are found to frequently recur, are not acceptable and will require immediate action by the Sponsor. Frequent non-compliances could potentially be classified as a serious breach.

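### The set labelled ITT drops randomised patients later found ineligible, and the open-label protocol does not require that removal be judged on pre-randomisation data, blind and equally in all arms

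*Protocol*

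**What the plan says.** Protocol Section 9.4, Table 3, defines the ITT set as "All patients who are randomised and match the inclusion/exclusion criteria of the Master Protocol and relevant sub protocol". The synopsis, under Analysis sets, agrees: "All patients who are randomised and match the inclusion/exclusion criteria of the Master Protocol and relevant sub-protocol will be included in the ITT".

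Table 4 in Section 9.5.1 ties the primary analysis to this set. For Stage 1: "Patients in the Stage 1 Intention to Treat (ITT) set will be used". For Stage 2: "Patients in the Stage 2 ITT set will be used for the following analyses". Table 3 lists no efficacy set made up of all randomised patients.

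Three other passages bear on how the definition would work:

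- Section 6.3: "No blinding will be used in this study".
- Section 5.0: "Prospective approval of protocol deviations to recruitment and enrolment criteria, also known as protocol waivers or exemptions, is not permitted".
- Appendix 2, Protocol Compliance: "Accidental protocol deviations can happen at any time".

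**The concern.** An intention-to-treat set normally keeps every randomised patient, because only that comparison is protected by randomisation. Here membership has a second condition, eligibility. If the condition is settled after allocation, the set can be altered by knowledge or events that follow allocation.

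The category is not empty. Deliberate waivers are barred, but the protocol accepts that accidental deviations occur, and enrolling an ineligible patient is one of them.

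Some entry criteria leave room for later judgement. Section 5.2 excludes "Any patient whose interests are not best served by study participation, as determined by a senior attending clinician". It also lists anticipated transfer, allergy to a study medication and experimental off-label treatment for COVID-19. An allergy could come to light at dosing, and SoC patients never receive the candidate agent.

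At stake is the validity of the Stage 1 comparison that informs progression and of the confirmatory Stage 2 test. If patients with a poor outlook were removed more often from one arm, that arm would look better with no drug effect.

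**Working it through.** **1. Does the text require removal after randomisation?** Table 3 and the synopsis impose two conditions: randomised, and eligible. A patient randomised in error meets the first and fails the second, so is removed. Table 4 applies the set to both primary analyses. The protocol nowhere limits this judgement to pre-randomisation data, nowhere requires it to be made blind to arm and outcome, and nowhere requires equal application across arms.

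**2. The plan's own figure.** Inputs from Section 9.3: Day 29 response 85.5% against 70%, one-sided alpha 0.025, power 90%, 126 per arm, 188 events.

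- Implied HR = ln(1 − 0.855)/ln(1 − 0.70) = ln(0.145)/ln(0.30) = 1.604.
- Schoenfeld events = 4(1.960 + 1.282)²/(ln 1.604)² ≈ 188.3, or 189 rounded up. With HR 1.6 the answer is 191.
- The stated 188 reproduces, and power at 188 events and HR 1.6 is 0.897.

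**3. Size of a possible bias in Stage 2.** The documents give no removal rate, so these inputs are assumed: no drug effect, 70% response in both arms, a fraction x removed from the candidate arm only, and response q among those removed.

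- Apparent candidate-arm response: p = (0.70 − xq)/(1 − x)
- Apparent HR = ln(1 − p)/ln(0.30)
- One-sided error = 1 − Φ(1.96 − ln(HR)·√188/2)

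Worked case, x = 0.05 and q = 0.30: p = (0.70 − 0.015)/0.95 = 0.721; HR = ln(0.279)/ln(0.30) = 1.060; ln(HR)·√188/2 = 0.0587 × 6.856 = 0.402; error = 1 − Φ(1.558) = 6.0%.

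| Removed, candidate arm only | Response among those removed | Apparent response | Apparent HR | One-sided error |
|---|---|---|---|---|
| 0% | – | 70% | 1.00 | 2.5% |
| any x | 70% (unrelated to prognosis) | 70% | 1.00 | 2.5% |
| 1% (about 1 of 126) | 40% to 30% | 70.3–70.4% | 1.008–1.011 | 2.9–3.0% |
| 2% (about 3 of 126) | 40% to 30% | 70.6–70.8% | 1.017–1.023 | 3.3–3.6% |
| 5% (about 6 of 126) | 40% to 30% | 71.6–72.1% | 1.045–1.060 | 4.9–6.0% |

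If equal fractions with the same prognosis leave both arms, the apparent HR remains 1 and there is no inflation. The formula uses the planned 188 events. The null case itself yields 0.70 × 252 ≈ 176, so the table slightly overstates: with 176 events the 5% row becomes 4.8–5.8%.

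**4. Effect on power.** The stated numbers imply an event fraction of about 0.75 (188/252). With all 252 patients retained, 252 × 0.75 = 189 events and power is 0.898. If 2%, 5% or 10% of all patients were dropped, events would fall to about 185, 180 or 170 and power to 0.892, 0.883 or 0.865. The loss of power is small, so possible bias is the main issue.

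**The case against.** The strongest reply is that the protocol points to eligibility being settled before allocation, for everyone. Section 5.0 requires each patient to satisfy the Master Protocol and at least one sub-protocol before enrolment. Section 8.0 requires screening evaluations to be completed and reviewed. The Schedule of Activities places eligibility at screening and randomisation at baseline. Section 6.3 leaves a patient out of an arm only when ineligible for it, so eligibility for each agent must be known before allocation, including for patients who then receive SoC. Waivers are barred, and most criteria are objective baseline facts. This stands: late-found ineligibility should be uncommon, and nothing suggests it would fall mainly in one arm.

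A reader might infer more than the documents support. They do not say that set membership is decided by people who know the arm; the statement on blinding concerns treatment. Nor do they say that sub-protocol criteria are checked less carefully in SoC patients; the sections above suggest otherwise. And the reference to the relevant sub-protocol is not meaningless for a control: it can be read as the sub-protocol of the comparison being made. That restriction is proper in this platform, because a SoC patient who could never have been allocated to an agent does not belong in its comparison.

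Section 9.5 also leaves description of the analysis sets to the SAP, which is not shown and may contain safeguards. That does not answer the point. The protocol has already fixed the definition, and an SAP using all randomised patients would contradict Table 3.

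**Conclusion.** The point holds as a fault in a stated definition. The primary analysis set in both stages removes randomised patients for ineligibility found later, in an open-label trial, without the conditions that could make such removal defensible.

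The size of any bias cannot be derived from the documents. Zero is a legitimate value: Stage 2 one-sided error remains 2.5% when removal is balanced or unrelated to prognosis. Under the assumed removal from the candidate arm only, with 30–40% response among those removed, it is about 3% at 1%, 3.3–3.6% at 2% and 4.9–6.0% at 5%. These figures show sensitivity. They do not forecast what will happen, and a reader should not infer that error is in fact doubled.

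Correction is warranted because the definition governs the confirmatory test and the change is simple.

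**What to change.** In Table 3 and in the synopsis (Analysis sets), define the ITT set separately for each agent comparison as:

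- all patients randomised to that agent; and
- all concurrently randomised SoC patients recorded before allocation as eligible for that agent's sub-protocol;
- analysed as randomised, with no removal for ineligibility discovered later.

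Record each patient's eligibility for every open sub-protocol before allocation. Section 6.3 already needs this information to decide which arms a patient can enter. A bare definition of all randomised patients would not do, since read literally it would admit SoC patients who could not have been allocated to the agent.

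Keep the present eligibility-matched set as a supportive analysis, named per-protocol or modified ITT.

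The cost is two wording changes and a record of eligibility at randomisation. A few ineligible patients stay in the primary analysis, which may dilute the effect slightly. No sample size changes: 126 per arm still gives about 189 events and power of 0.898 at the implied event fraction of 0.75.

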## 9.5 Statistical Analyses

The Statistical Analysis Plan (SAP) will describe the patient analysis sets to be included in the analyses and procedures for accounting for missing, unused, and spurious data. Addenda to the SAP will be produced for each sub-protocol.

Efficacy, safety, PK, and pharmacodynamic results will be listed and summarised by stage (pilot stage; confirmatory stage), dose, and scheduled time for the respective analysis sets, where appropriate. Candidate agent concentration versus response variables may be graphically displayed for selected endpoints. Exposure-response data obtained from this study may be combined with data from other studies and used for modelling and simulations.

### 9.5.1 Efficacy Analyses

**Table 4 Efficacy Analyses**

| Endpoint    | Statistical Analysis Methods                                                                                                                                                                                                                                                                                                                                                                                                                                                                                                                                                                                                                                                                                                                                                                                                                                                                                                                                                                                                                                                                                                                                                                                                                                                                                                                                                                                                                                                              |
|-------------|-------------------------------------------------------------------------------------------------------------------------------------------------------------------------------------------------------------------------------------------------------------------------------------------------------------------------------------------------------------------------------------------------------------------------------------------------------------------------------------------------------------------------------------------------------------------------------------------------------------------------------------------------------------------------------------------------------------------------------------------------------------------------------------------------------------------------------------------------------------------------------------------------------------------------------------------------------------------------------------------------------------------------------------------------------------------------------------------------------------------------------------------------------------------------------------------------------------------------------------------------------------------------------------------------------------------------------------------------------------------------------------------------------------------------------------------------------------------------------------------|
| Primary     | 
Stage 1:
 
Time to 2-point improvement on the 9-point ordinal scale, live discharge, or fit for discharge (as analysed at Day 29), whichever comes first, will be compared with each treatment arm with standard of care (SoC) using log-rank test at the one-sided 0.1 alpha level. Patients in the Stage 1 Intention to Treat (ITT) set will be used.
 
Stage 2:
 
The time to 2-point improvement on the 9-point ordinal scale, live discharge, or fit for discharge (as analysed at Day 29), whichever comes first, analyses will be conducted between the selected treatments plus SoC and SoC alone. The primary endpoint could be re-determined based on Stage 1 results. Patients in the Stage 2 ITT set will be used for the following analyses:
 
The time to 2-point improvement on 9-point ordinal scale, live discharge, or fit for discharge at Day 29 will be conducted between each selected treatment group and control using the log-rank statistic, stratifying for study centre and baseline severity grade, and the p-value associated with the log-rank statistic will be compared at the 2-sided 0.05 alpha level. The hazard ratio between treatment arm and SoC will be estimated using Cox regression, including treatment, age category (age <70 years vs ≥70 years), baseline severity, age category and treatment interaction, baseline severity and treatment interaction as fixed effect, and study centre as random effect.
 |
| Secondary   | 
Stage 1:
 
2-point improvement on a 9-point ordinal scale will be analysed using CMH test, with stratification factors as covariates.
 
Time to live discharge.
 
Stage 2:
 
Binary endpoints, including response rates at Days 2, 8, 15, 22, and 29, and mortality rates at Days 15, 29, and 60, will be analysed using the same CMH test and logistic regression model as in the primary endpoint.
 
Time-to-event endpoints, including time to clinical improvement, time to death, and time to live discharge, from treatment start date will be plotted with Kaplan-Meier curves and will be tested with the log-rank test.
 
Other continuous endpoints will be summarised with descriptive statistics such as mean, standard deviation, median, minimum, and maximum.
                                                                                                                                                                                                                                                                                                                                                                                                                                                                                                                                                                                                                                                                         |
| Exploratory | Will be described in the Statistical Analysis Plan finalised before database lock                                                                                                                                                                                                                                                                                                                                                                                                                                                                                                                                                                                                                                                                                                                                                                                                                                                                                                                                                                                                                                                                                                                                                                                                                                                                                                                                                                                                         |

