#### Stage 1 (Pilot Stage)

This stage will focus on assessing a number of candidate agents with SoC, with the aim of carrying forward a subset of candidate agents into Stage 2, the confirmatory stage.

Approximately 60 patients will be randomised into each arm at this stage of the study, whereby patients will receive either one of the candidate agents (with SoC) or SoC alone. The chosen endpoint to compare treatments will be the time to a 2-point improvement on a 9-point category ordinal scale, discharge from hospital, or considered fit for discharge.

Based on the chosen endpoint, a preliminary analysis will be carried out when an estimated 81 events have been observed across each agent treatment and SoC or 28 days after the last patient has been randomised, whichever occurs sooner, as determined by the IDMC. In order to achieve this number of events, it is expected that 54 patients are needed per arm, which will provide 80% power to detect a hazard ratio of 1.6 for the occurrence of the event, when comparing each candidate agent with SoC. This calculation is based on a 1-sided test and a 10% significance level, and assumes 85.5% of patients will improve, be discharged from hospital, or considered fit for discharge at Day 29 for a candidate treatment versus 70% of patients for the SoC (the estimate of SoC was taken from Cao 2020^4). To allow for uncertainty in the recruitment rates, it is expected that up to 60 patients (rather than 54 patients) will be randomised to each arm in order to achieve the required number of events for the preliminary analysis.

Safety data will also be assessed.

Full details will be provided in the IDMC charter.

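### The Stage 1 primary log-rank test names no strata although randomisation is stratified by severity grade; stratifying by grade alone would make it less conservative and somewhat more powerful

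*Protocol*

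**What the plan says.** In Table 4 (Protocol, Section 9.5.1) the Stage 1 primary endpoint "will be compared with each treatment arm with standard of care (SoC) using log-rank test at the one-sided 0.1 alpha level". No stratification factor is named.

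Three other places bear on this:

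- Section 6.3: "Randomisation will be stratified by study centre and baseline severity grade".
- Table 4, Stage 2 primary analysis, in the same cell and on the same endpoint: each comparison is made "using the log-rank statistic, stratifying for study centre and baseline severity grade".
- Table 4, Stage 1 secondary analysis: 2-point improvement is analysed by a CMH test that uses the stratification factors.

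The sample size text in Section 9.3 says "it is expected that 54 patients are needed per arm, which will provide 80% power to detect a hazard ratio of 1.6". It adds "This calculation is based on a 1-sided test and a 10% significance level", and the calculation "assumes 85.5% of patients will improve, be discharged from hospital, or considered fit for discharge at Day 29 for a candidate treatment versus 70"% for SoC. These are overall rates, not rates by grade.

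**The concern.** Patients enter at Grades 3 to 5 (Section 5.1), and the response rule in Section 8.1.1 sets a different hurdle for each grade. A Grade 3 patient responds on moving one point to Grade 2, through the fit-for-discharge rule. A Grade 4 patient needs two points and must also reach Grade 2. A Grade 5 patient responds at Grade 3, still in hospital. Baseline grade is thus built into the event as well as being a likely prognostic factor.

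Balancing the arms on a prognostic factor and then leaving it out of the test has two known effects. The unstratified variance still counts the between-grade variation that randomisation has removed from the arm difference, so the test rejects too rarely under the null. In addition, mixing grades with different hazards pulls the overall hazard ratio towards 1 as the faster responders leave the risk set. Both reduce the chance that a useful agent meets the Stage 1 threshold, although the grade is already recorded.

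**Working it through.** **1. Reproduce the stated design.** Inputs from Section 9.3: HR 1.6, one-sided alpha 0.10, power 80%, 1:1 allocation.

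- Schoenfeld: events = 4(z₀.₉₀ + z₀.₈₀)² / (ln 1.6)² = 4(1.2816 + 0.8416)² / 0.4700² = 81.6, so 82 (stated 81).
- Power with 81 events = Φ(√81/2 × 0.4700 − 1.2816) = Φ(0.833) = 79.8%.
- Mean response = (0.70 + 0.855)/2 = 0.7775. Patients per arm = 82/0.7775/2 = 52.7, so 53 (stated 54).
- HR implied by the overall rates = ln(0.145)/ln(0.30) = 1.604.

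The design reproduces within rounding. The 1.6 matches the overall rates, with no allowance for differences between grades.

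**2. Compare the two tests.** The protocol gives neither a grade mix nor a grade effect, so both are assumed. Simulation: 4000 trials per scenario, 54 per arm, exponential times recorded daily and censored at 28 days, SoC response held at 70% overall, grades exactly balanced between arms, one-sided 0.10. In the scenarios tabulated with HR 1.6 within grade, expected events are about 81-84, close to the planned trigger. Monte Carlo standard error: √(0.8 × 0.2/4000) = 0.6 points for power and √(0.1 × 0.9/4000) = 0.5 points for type I error.

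Each cell shows unstratified vs grade-stratified, first for equal thirds of Grades 3/4/5, then for a 20/50/30% mix.

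| Hazard multipliers, Grades 3/4/5 | Power, HR 1.6 within each grade | Power, overall rates 70% vs 85.5% | Type I error |
|---|---|---|---|
| 1/1/1 | 80.2 vs 80.0; 81.6 vs 80.5 | 81.3 vs 80.6; 80.2 vs 80.0 | 9.8 vs 10.0; 10.5 vs 10.3 |
| 1.5/1/0.67 | 77.8 vs 80.3; 78.8 vs 80.3 | 83.0 vs 85.4; 83.2 vs 84.3 | 8.9 vs 9.6; 8.8 vs 9.6 |
| 2/1/0.5 | 71.6 vs 78.4; 74.6 vs 79.7 | 85.8 vs 91.0; 84.6 vs 88.7 | 7.7 vs 9.9; 8.2 vs 10.0 |
| 3/1/0.33 | 58.6 vs 78.4; 67.0 vs 79.4 | 90.9 vs 98.1; 88.0 vs 95.5 | 5.2 vs 10.8; 6.5 vs 10.1 |

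A third assumed mix (30/50/20%) was simulated separately. With multipliers 1.5/1/0.5, power at HR 1.6 within grade is 76-77% vs 79-80%; with 2/1/0.37 it is 70-72% vs 79%. Unstratified type I error is about 9% and about 7%. At the overall rates of 70% and 85.5%, the unstratified test has about 84-90% power and the stratified test about 87-93%.

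**3. Why the two power columns differ.** Holding SoC at 70% and fixing HR 1.6 within grade lowers the overall experimental rate below the planned 85.5%: to 84.4% or 84.7% in the second row, 82.7% or 83.5% in the third, and 80.3% or 81.6% in the fourth. Keeping 85.5% requires a within-grade HR of 1.67 or 1.65, 1.81 or 1.74, and 2.11 or 1.93 respectively. The shortfall below 80% therefore belongs to a smaller effect than the overall rates describe. The gain from stratifying appears in both columns.

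**4. Adding centre.** About 18 centres (Section 4.1) × 3 grades = 54 cells for 2 × 54 = 108 patients, or two per cell on average. Many cells then hold one arm only and contribute nothing. Simulated power is 52-56% when patients fall into 18 centres at random, and 62-67% in a separate simulation under other assumed values.

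**The case against.** A reader might infer that the stated 80% power is lost. The protocol does not support that: Section 9.3 derives the 80% from overall rates, and under those rates the unstratified test stays at or above 80% in every scenario examined. A shortfall needs 1.6 to be read as the within-grade effect, which the protocol does not say.

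A reader might also infer that effective agents will be wrongly dropped. Section 9.6 rests progression on the totality of data as judged by the Steering Committee, and the Stage 1 CMH analysis already uses the stratification factors. The log-rank test is one input, though it is the primary Stage 1 analysis and the basis of the sample size.

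Nor does it matter much that the two stages would test slightly different quantities. Stage 1 patients are not carried into Stage 2, and the Stage 2 endpoint and analysis may be re-selected.

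Two further objections have weight. The gradient is assumed, and the easier target for Grade 5 could offset a worse prognosis; with no gradient there is nothing to gain. The protocol also never uses the word unstratified, and a statistical analysis plan may name the strata. But Table 4 does name them for the neighbouring analyses, so its silence on the Stage 1 primary test reads as a choice and should be aligned.

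**Conclusion.** The point stands as an avoidable inefficiency and an internal mismatch, not as a failure of the stated power. If grade is prognostic, the Stage 1 test as written is conservative, with type I error about 7-9% against 10% under the moderate and strong gradients assumed. It is also less powerful than a grade-stratified test at 54 per arm. The gain from stratifying is about 2-4 points for a moderate gradient (about 1 in the mildest case) and about 4-9 for a strong one; it is larger with 3-fold steps between grades. If grade has no effect, stratifying costs at most 1-2 points.

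All these sizes rest on an assumed grade mix, assumed hazards by grade and exact balance of grades between arms. Only the direction follows from the design itself.

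**What to change.** In Table 4, Stage 1 primary analysis, specify a *log-rank test stratified by baseline severity grade*, and report the Stage 1 hazard ratio from a Cox model stratified by, or adjusted for, grade.

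Do not carry over the Stage 2 wording. Stratifying by centre as well would cost far more power at this size than grade stratification gains.

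The cost is a short text change. Grade is already collected and used in randomisation, so no new data are needed and the planned number of events can stay as it is.
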